## Background

The most common psychopathologies in early childhood are regulatory disorders (e.g. excessive crying, sleeping and feeding disorders), which affect about 20% of all infants and toddlers [1]. Fortunately, the majority of these early mental health problems are transient. Yet there are major gaps in improving clinical outcome and development, in (1) adequate assessments of early psychopathological signs [2, 3] due to a lack of validated assessment methods, and (2) detection of severe clinical courses and subsequent treatment [1, 4]. The distribution of psychopathology seems to correspond with later developmental stages, but the description of symptoms in the early years of life do not fit within the framework of the common diagnostic classification systems of ICD-10 and DSM-V. Only in the last couple of years has the focus of research in this field shifted to diagnostic criteria for infants, with the development of the Diagnostic Classification of Mental Health and Developmental Disorders of Infancy and Early Childhood DC: 0–5™ [5].

A meta-analysis by Hemmi and colleagues [1] showed that parental mental health problems (e.g. depression, anxiety, obsessive-compulsive disorders) are potential risk factors for infant psychopathology. Moreover, Fraiberg, Adelson and Shapiro [6] underline the problem of transmission in parenthood in their concept of the ‘Ghosts in the nursery’. They explain the negative impact on parental functions using their own transgenerational experience when raising their children [6, 7]. The development of a strong, stable bond between mother and child is one of the most essential factors for an infant’s resilience and healthy development [8, 9]. Maternal sensitivity is well known to be a key factor in the mother-infant interaction and the development of a secure attachment to the mother [8–10].

Psychodynamic Parent-Infant Psychotherapy (PIP) within dyadic or triadic sessions aims to improve maternal sensitivity and attachment security [11]. Various studies have already demonstrated the efficacy of PIP in (1) reducing psychological symptoms (e.g. [12]), (2) improving maternal sensitivity (EAS), and (3) improving attachment security in high-risk samples [11, 13] compared with control groups and diverse interventions (e.g. education, support and medication) [11, 14, 15].

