### Trial design

The two-armed, open, randomised, controlled multicentre study with parallel groups and blinded endpoint assessment (PROBE design; prospective randomised, blinded endpoint) with a six-week intervention is currently underway in Leipzig, Berlin, Potsdam and Hamburg. All study centres and participating clinics there provide focused and supervised certified PIP in accordance with a previously elaborated SKKIPPI Study Manual ([name], [name], [name]: SKKIPPI Study manual for Parent-Infant-Toddler Psychotherapy (PIP), Unpublished). Depending on the severity of the child’s pathological symptoms, and in agreement with parental preferences, a decision is made on treatment setting (in−/outpatient) before randomisation. Participants are then randomly assigned to either PIP or CAU, and data are collected at three measurement points: at baseline before intervention, immediately after treatment, and at 12 months follow-up. The biostatistician of the Institute for Social Medicine, Epidemiology, and Health Economics at the Charité – Universitätsmedizin Berlin generates the allocation sequence based on a computer generated random list, applying a 1:1 block randomisation with variable block length and stratified by setting (inpatient/outpatient) and study centre. Mother-child dyads are randomly assigned to either PIP or CAU.

Before being enrolled in the trial, participants are screened by a professional physician or psychotherapist for eligibility and clinical diagnoses. Only children receiving an ICD-10 diagnosis of regulatory disorder can take part in the study. Eligible mothers of these children are informed verbally about the study, and written informed consent must be given before randomisation. Afterwards, baseline assessments are carried out, and the 6 weeks of interventions start. At the end of treatment, participants are assessed again, as well as 12 months after baseline. Mothers will receive €100 as monetary compensation (25€ after Baseline, 25€ after 6 weeks follow-up and 50€ after the last assessment) until the 12-months follow-up. Throughout the study, the study nurse is in contact with the participants via phone calls or e-mails to schedule appointments. Treatment allocation is masked to the assigning personnel and there are no special criteria for discontinuing or modifying the allocated intervention (Fig. 1).

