### Participants and eligibility screening

We include infants and young children aged 36 months or younger (Table 1). Participation is conditional upon written informed consent from the legal guardians. All participants are carefully informed about the study goals and assessment.

**Table 1 Tab1:** Inclusion and exclusion criteria

Inclusion criteria	
• Infants aged 36 months or younger	
• Infants diagnosed (by a certified paediatrician, psychiatrist or psychotherapist) with at least one regulatory disorder	
• Mothers must speak German to a sufficient level and understand the aims of the study	
• Mothers must be in a psychological state that allows them to participate in the study	
Exclusion criteria	
• Mother or child is already participating in other clinical trials	
• Mother or child is receiving any other form of psychotherapy	
• Mother is dealing with acute substance abuse, or has suicidal tendencies or acute psychosis	
• Child has a suspected alcohol embryopathy, or severe organic impairments	

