### Secondary outcomes

#### Child attachment

The most important secondary outcome will be the child’s attachment style, measured using the Strange Situation Procedure (SSP) for children up to 20 months [31]. The SSP is a standardised procedure recording eight episodes to rate the child’s attachment quality to his or her caregiver. Attachment security is rated by independent coders blind to treatment allocation. The classification can be secure (B), avoidant (A), or ambivalent (C). Disorganised (D) attachment qualities will also be scored.

The attachment style of children older than 20 months is assessed using Attachment Q-Sort (AQS) [32]. The AQS evaluates the degree of attachment security for infants aged 12 to 48 months, and is a one- to two-hour procedure in which the child and its mother are observed in their home environment. The infant’s behaviour is evaluated by the observer for 90 standardised Q-Sort items, which are compared to a typical profile of securely attached children. The AQS varies on a scale between − 1 and 1, and does not reflect the variety of attachment categories, as the SSP does.

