#### Primary endpoint

The primary analysis of the primary endpoint (maternal sensitivity measured using the EAS subscale after 6 weeks) will be analysed using ANCOVA based on the FAS population using PIP versus CAU as the factor treatment group, EAS sensitivity at baseline as covariate, and the stratification variable treatment setting. Results will be displayed as adjusted means of the treatment group together with 95% confidence intervals and the respective *p* value (two-sided). The significance level is set at α =0.05. All further analysis is considered exploratory.

A secondary analysis of the primary endpoint will also be carried out using the ANCOVA model based on the PP population. Additional moderator analyses of the efficacy of PIP for a change in maternal sensitivity (EAS) will be conducted with treatment setting as the moderator, i.e. by additionally adding a ‘treatment group’ * ‘treatment setting’ interaction term to the model. Further moderator analyses regarding the efficacy of PIP will comprise maternal attachment type (AAI attachment) or maternal reflective functioning (AAI RF) as moderators.

In addition, models incorporating multiple imputation methods based on the PP population and a hierarchical regression model (including the therapist as a grouping factor and therapist’s adherence as covariate) will be used for sensitivity analyses of the primary outcome. To investigate the longitudinal change of the primary endpoint, linear mixed models (LMMs) incorporating both measurement points for each outcome (FAS population) will be computed. To explore further effects of additional predictors (such as the therapists carrying out the interventions), the models will be compared based on model fit values (AIC, the Akaike Information Criterion), with these predictors included in the model term.

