#### Secondary endpoints

Primary analyses of the secondary endpoints replicate the computation of the models for the primary endpoint, as either ANCOVAs or logistic regressions (depending on the continuous or dichotomous scale of the respective endpoint). Group differences in the children’s attachment organisation (SSP/ AQS, binarised evaluation: secure/ insecure attachment), as well as all responder analyses (EAS sensitivity, EPDS, PRFQ, PSI at T1 and T2; SFS at T1, CBCL at T1 and T2), will be computed as logistic regressions adjusted for the stratification variable treatment setting with presentation of odds ratios. Should no cut-off values be available, dichotomous response variables for these measures will be computed using the Reliable Change Index (RCI; RCI > 1.96) [45]. Linear mixed models will be used to analyse the change in the secondary endpoints (maternal stress level, reflective functioning (PRFQ), and infantile symptoms) during the course of the study (12-months follow-up) across all measurement points.

Additional sensitivity analyses will be performed for health economic parameters as secondary endpoints, varying unit-cost assumptions for documented health care utilisation within realistic ranges. All secondary analyses of the primary and secondary endpoints are considered exploratory.

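### Free improvement: the stated models omit child age. The cost is small for the primary ANCOVA but larger for the attachment endpoint, where age decides the instrument.

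*Protocol article*

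**What the plan says.** All references are to the protocol article.

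- **Primary endpoint:** the ANCOVA uses treatment group, "EAS sensitivity at baseline as covariate, and the stratification variable treatment setting".
- **Secondary endpoints:** "Primary analyses of the secondary endpoints replicate the computation of the models for the primary endpoint, as either ANCOVAs or logistic regressions". The attachment comparison and all responder analyses "will be computed as logistic regressions adjusted for the stratification variable treatment setting with presentation of odds ratios".
- **Participants and eligibility screening:** "We include infants and young children aged 36 months or younger".
- **Trial design:** randomisation is "stratified by setting (inpatient/outpatient) and study centre". Follow-up ends 12 months after baseline.
- **Child attachment:** attachment is ranked first among the secondary outcomes. It is "measured using the Strange Situation Procedure (SSP) for children up to 20 months", and by the Attachment Q-Sort (AQS) in older children. The section adds that the AQS score, which runs from -1 to 1, does not capture the range of attachment categories that the Strange Situation Procedure (SSP) does.
- **Primary endpoint and Secondary endpoints:** everything beyond the primary analysis is labelled exploratory.

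Child age appears in none of the stated models.

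**The concern.** A 0 to 36 month range is wide for outcomes measured on the child. The document itself ties several instruments to age: the attachment measure changes at 20 months, the CBCL is linked to 18 months, and the ET 6-6 R starts at 6 months. If age predicts an outcome and is not in the model, its variance stays in the residual and intervals are wider than they need be. A chance age difference between arms is then left uncorrected in the observed estimate.

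Attachment is the sharpest case. The Aims and hypotheses section expects more securely attached children at 12 months. A child's entry age largely settles which of two different instruments yields the secure/insecure label at that visit. The two are pooled in one logistic model with neither age nor instrument as a term, and the text describes no baseline attachment score.

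There is also a question of timing. The plan compares arms for baseline differences but gives no rule for acting on them, and it lets further predictors enter by AIC comparison. If an age imbalance appears, any adjustment would be chosen after seeing it.

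**Working it through.** **Inputs from the document:** d = 0.64, two-sided alpha 0.05, 64 evaluable dyads per group at a stated 90% power, 20% dropout, 80 randomised per group (Sample size considerations); entry at 0 to 36 months; instrument change at 20 months; last visit 12 months after baseline.

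**Assumptions (not in the document):** the share R² of residual variance that age explains beyond the other covariates; entry age uniform on 0 to 36 months; d expressed in residual SDs; the 20-month limit applied to age at the 12-month visit.

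**1. The plan's own figure.** n per group = 2(1.960 + 1.282)² / 0.64² = 51.3, so 52 (53 with the t distribution), not 64. With 64 per group, power at d = 0.64 is 94.9%. The dropout step reproduces: 64 / 0.8 = 80. The mismatch in n does not bear on the age question; it only means that the comparison below starts from 94.9%.

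**2. Primary ANCOVA.** Adding age multiplies the SE by √(1 − R²). Power is from the noncentral t with noncentrality [0.64 / √(1 − R²)] × √(64/2). The SD of the shift due to chance age imbalance, when age is left out, is √R² × √(2/64) residual SDs.

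| Assumed R² | SE ratio | Power, age omitted | Power, age included | SD of chance shift |
|---|---|---|---|---|
| 0.01 | 0.995 | 94.9% | 95.1% | 0.018 |
| 0.04 | 0.980 | 94.9% | 95.6% | 0.035 |
| 0.09 | 0.954 | 94.9% | 96.5% | 0.053 |
| 0.20 | 0.894 | 94.9% | 98.0% | 0.079 |

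The low rows are the relevant ones for the primary outcome, because baseline sensitivity on the same scale absorbs any age effect already present at baseline. Even in the last row, the chance shift is small against 0.64.

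**3. Validity of the primary test.** A simulation used 10,000 runs per scenario, 64 per arm, uniform age, age-baseline correlation 0.3, baseline-outcome correlation 0.5 and partial age-outcome correlation 0.1 to 0.3. Type I error was 5.1% to 5.2% without age and 5.0% to 5.1% with it. The mean estimate was about 0.572 either way for a true 0.573.

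**4. Attachment.** A child is over 20 months at the 12-month visit if entry age exceeds 20 − 12 = 8 months. Under uniform entry age the AQS share is (36 − 8)/36 = 77.8%. The SE of the between-arm difference in that share is √(2 × 0.778 × 0.222 / 64) = 0.0735, and 1.96 × 0.0735 = 0.144, or about 14 percentage points. If the true share were 50% or 90%, the same formula gives about 17 or 10 points.

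The effect on the result depends on how far the proportion rated secure differs between instruments, which the document does not give. If it differed by 10 or 20 points (assumed), a 14.4-point imbalance would move the difference between arms by 0.144 × 10 = 1.4 or 0.144 × 20 = 2.9 points.

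**The case against.** The strongest reply is that treatment, baseline and setting form a valid prespecified model, and leaving out a prognostic covariate is not an error. That stands. Randomisation keeps the estimate unbiased, and the interval already allows for chance imbalance. The age-linked evidence in the document concerns child measures; nothing in it says that maternal sensitivity depends on child age once baseline is known. A reader might infer that age imbalance passes directly into the primary estimate. The document does not support that, because baseline sensitivity is in the model.

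A reader might also infer that the 6-week crying, feeding and sleeping questionnaire (SFS) has no baseline score to absorb age. That cannot be asserted. The assessment schedule (Fig. 3) is not shown, and the Secondary endpoints section plans mixed models of infant symptoms over all time points and a reliable change index where cut-offs are lacking, which implies pre-scores. Nor does the Background remark "Fortunately, the majority of these early mental health problems are transient" show age dependence: it describes the course of the problems, not how scores vary with age.

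Finally, the child-outcome analyses are exploratory, and an analysis plan that is not shown may add covariates. This lowers the priority. It does not answer the attachment point, because the article does state that model's adjustment and pools two instruments without a term for either age or instrument.

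**Conclusion.** This is a free improvement, not a defect in the primary analysis. For the primary ANCOVA, adding age would cut the SE by about 0.5% to 2% and add about 0.2 to 0.7 power points at d = 0.64, on an assumed R² of 1% to 4%. The document gives no correlation between age and outcome, so these figures show a range and are not estimates.

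The case is stronger for child outcomes and strongest for attachment. Under uniform entry age, about 78% of children would be rated by the AQS, and the arms could differ in that share by about 14 points by chance. How much this moves the treatment effect depends on an unknown difference between instruments. In a logistic model, omitting a prognostic covariate also changes which odds ratio is being estimated, so the choice should be made in advance.

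**What to change.** Before unblinding, prespecify the following:

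- Child age at randomisation (continuous) as a covariate in every child-outcome model: the ANCOVAs, the mixed models, and the attachment and responder logistic regressions.
- In the attachment model, also instrument (SSP or AQS), or else the treatment effect reported separately by instrument. State that the adjusted odds ratio is conditional on these terms.
- Age as a linear covariate in the primary ANCOVA, or in a named sensitivity analysis of it. A quadratic term is optional.

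The cost is one sentence in the plan and one or two degrees of freedom out of about 125. No new data are needed, because age is an entry criterion and so is known for every dyad.

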### Data analyses

#### General considerations and socio-demographic data

Socio-demographic and clinical information are described at baseline using frequencies and percentages (e.g. categorical variables) or means and standard deviations (e.g. continuous variables), and treatment conditions compared to assess potential baseline differences. The statistical analyses are based on all mother-child dyads included in the study after randomisation (Fig. 1), according to ITT (Intention to Treat) principles. The data to be used in all analyses (unless otherwise stated) is defined as the Full Analysis Set (FAS) and includes all mother-child dyads after randomisation, irrespective of the treatment received. Data from mother-child dyads who drop out of the study are included in the FAS up to the date they withdraw. The Per Protocol (PP) population is a subset of the FAS and includes mother-child dyads who conform to the study plan (i.e. sufficient treatment adherence, no major protocol violations). The safety population is defined as mother-child dyads who have participated in at least one intervention session, and is analysed according to the treatment they received.

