#### Missing data

After written informed consent and randomisation, participants can be excluded from the analyses only if there has not been any intervention, no data have been collected after randomisation, or at the participants’ express request after withdrawing from the study during the data collection phase. Primary statistical analyses of the primary and secondary endpoints are based on the FAS population without the imputation of missing data. For a sensitivity analysis, missing values for the primary endpoint will be imputed using Multiple Imputation methods for linear regression based on Markov chain Monte Carlo (MCMC) simulations. Imputation variables will be selected blinded for the intervention groups, and at least 5000 iterations and 100 imputations will be calculated.

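### The multiple-imputation check on the primary endpoint is set on the Per Protocol population, so it cannot show whether the unimputed FAS result is robust to missing outcomes

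*Protocol article*

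**What the plan says.** All references are to the Protocol article.

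- **Primary analysis.** Under Primary endpoint, 6-week EAS sensitivity is analysed by ANCOVA on the FAS, with treatment group, baseline sensitivity and treatment setting. Under Missing data, the primary analyses "are based on the FAS population without the imputation of missing data".
- **Sensitivity analysis.** Under Primary endpoint, the sensitivity analyses of the primary outcome include "models incorporating multiple imputation methods based on the PP population".
- **Same analysis, other section.** Under Missing data: "For a sensitivity analysis, missing values for the primary endpoint will be imputed using Multiple Imputation methods for linear regression". No population is named there. The section adds: "Imputation variables will be selected blinded for the intervention groups".
- **Analysis sets.** Under General considerations and socio-demographic data, the FAS is the default set unless stated otherwise and holds all randomised dyads. On drop-outs: "Data from mother-child dyads who drop out of the study are included in the FAS up to the date they withdraw". On the PP set: "The Per Protocol (PP) population is a subset of the FAS and includes mother-child dyads who conform to the study plan", explained there as sufficient adherence and no major violations.
- **Other models of the primary endpoint.** A PP ANCOVA as a secondary analysis, and linear mixed models on the FAS for longitudinal change.
- **Planned loss.** Under Sample size considerations, 64 per group is raised to 80 per group for 20% drop-out.

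**The concern.** A dyad without a 6-week video rating cannot enter an ANCOVA that imputes nothing, so the primary analysis is in effect a complete-case analysis of the FAS. A missing-data sensitivity analysis should then hold the population and the question fixed and vary only how the missing outcomes are handled. Here the population changes as well. PP membership is settled after randomisation, by adherence and violations, and dyads that leave during a 12-session course are likely to be among those who fail it. The imputation may therefore set aside some of the dyads it ought to represent.

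At stake is how the result is read. If the PP imputation agrees with the primary result, a report could call the finding robust to missing data when the FAS result has not been put to that test. If it disagrees, nobody can say whether population or missingness is the reason.

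**Working it through.** **1. The plan's own figure.** Inputs: 64 evaluable dyads per group and 20% drop-out (Sample size considerations).

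- 64 / (1 − 0.20) = 80 per group, 160 in total. The stated figure reproduces.
- Expected without the 6-week value: 0.20 × 160 = 32 dyads, leaving 160 − 32 = 128.

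This takes each drop-out as lacking the primary endpoint and staying in the FAS. The Missing data section allows a few exclusions after randomisation, which would lower the 32.

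**2. How many of the 32 a PP-based imputation covers.** PP is defined by adherence and violations, not by having an outcome, so the number is 32 × (1 − share of missing dyads that also fail PP). The protocol does not give that share, so the full range is shown.

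| Share failing PP (assumed) | Imputed in PP | Imputed in FAS |
|---|---|---|
| 0% | 32 | 32 |
| 25% | 24 | 32 |
| 50% | 16 | 32 |
| 75% | 8 | 32 |
| 100% | 0 | 32 |

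Even in the first row, dyads excluded from PP with an observed outcome are absent, so the analysis is still not one of the FAS.

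**3. What the comparison can identify.** Let A be the FAS ANCOVA without imputation (primary), B the FAS with imputation, C the PP ANCOVA without imputation, and D the PP set with imputation.

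- The question about the primary result is B − A.
- The plan supplies A, C and D, and D − A = (C − A) + (D − C): a population change plus an imputation change.
- D − C isolates imputation, but only inside PP. B does not appear, so B − A cannot be obtained.

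**4. Illustration by simulation.** Assumptions, none of them from the protocol except the 0.64 and the 20%: 1,000,000 dyads per scenario; about 27% non-adherent, with a severity factor driving both non-adherence and outcome; effect 0.64 in adherent dyads and 0 in the others; 20% of outcomes missing, with the probability depending on adherence only; PP taken as the adherent dyads of both arms.

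| Share of missing outcomes from non-adherent dyads | Full FAS effect | FAS complete-case | Difference | PP, all missing values perfectly recovered | PP complete-case |
|---|---|---|---|---|---|
| 25% | 0.469 | 0.465 | −0.004 | 0.643 | 0.643 |
| 50% | 0.469 | 0.507 | 0.038 | 0.640 | 0.640 |
| 75% | 0.467 | 0.544 | 0.077 | 0.640 | 0.640 |
| 90% | 0.472 | 0.570 | 0.098 | 0.640 | 0.640 |

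The error in the FAS complete-case estimate runs from about zero to about 0.10, while even a perfect imputation within PP stays at 0.64. The sizes belong to these assumptions. What is general is that the PP analysis does not respond to the bias it is meant to detect.

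**The case against.** **The Missing data section can be read as FAS.** It describes the imputation straight after a sentence about the FAS, names no population, and the FAS is the default. This stands in part: the two sections are not aligned. But the default yields where another set is stated, and the Primary endpoint section states PP. At best the population is ambiguous, which needs the same correction.

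**The FAS mixed model already covers missing outcomes.** It can keep dyads with only a baseline value, so a reader who inferred that missingness in the FAS is never examined would go too far. Its stated purpose is longitudinal change, however, and with one baseline and one 6-week value it rests on much the same missing-at-random assumption as the ANCOVA. It does not replace the check.

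**Imputation on the FAS is also missing-at-random.** This stands. With only the ANCOVA covariates in the imputation model it would essentially return the complete-case estimate. The gain comes from auxiliary variables, and informative drop-out would remain untested. It would still address the right population, which the PP version does not.

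**Two stronger readings do not hold.** A reader might infer that the PP imputation fills in almost nobody. PP is not defined by an observed outcome, so a dyad that attended its sessions but missed the recording could stay in PP and be imputed. A reader might also infer from "Imputation variables will be selected blinded for the intervention groups" that treatment arm is left out of the imputation model. That sentence says how variables are chosen, not that arm is omitted, and the detailed model may properly sit in an analysis plan that is not shown.

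**It is only exploratory.** Correct: the protocol calls everything beyond the primary analysis exploratory. That limits the severity but does not remove the point.

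**Conclusion.** The point holds in a limited form. The protocol sets its only stated imputation analysis of the primary endpoint on the PP population, while the primary result is an unimputed FAS ANCOVA with about 32 of 160 outcomes (20%) expected to be missing. Because population and missing-data method change together, neither agreement nor disagreement with the primary result tells whether the FAS result is robust to missing outcomes. This follows from the definitions of the sets and needs no numerical assumption.

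The number of missing dyads the PP version would impute cannot be fixed from the document; it lies between 0 and 32. The primary estimate, alpha and sample size are not affected. This is a should-fix.

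**What to change.** In both Primary endpoint and Missing data, state that the multiple-imputation sensitivity analysis is run on the FAS, meaning all randomised dyads. State that the imputation model contains the ANCOVA terms (treatment arm, treatment setting and baseline EAS sensitivity) plus auxiliary variables, and that the blinded selection applies to the auxiliary variables. Keep any PP imputation as a labelled supplement, to be read against the PP ANCOVA rather than against the primary result.

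Cost: a wording change in two sections and the same code run on another set, with slight extra analysis work. The interval in this sensitivity analysis may be somewhat wider. The sample size does not change. The change should be made before allocation is unblinded.
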